#### Key secondary endpoint

The key secondary endpoint is the extent of organ failure (Table 1) indicated by both:The mean Sequential Organ Failure Assessment (SOFA) score over the first 7 days following randomization with day 1 (d1) indicating the day of study inclusion (i.e., the day of the intervention). The SOFA score [13] will be recorded daily at inclusion and following the next 7 days.Organ support-free days (total days free of invasive ventilation, vasopressors / inotrops and RRT) until day 28.

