#### Study procedure (treatment arm): therapeutic plasma exchange (TPE)

The TPE treatment will be initiated within 6 h after randomization. Duration of TPE treatment is approximately 120–180 min. An additional second TPE can be performed at 24 h following randomization if the patient has responded to first treatment as indicated by any reduction of NE dose *and* if NE dose is still ≥ 0.4 µg/kg/min after 24 h. Both unfractionated heparin (UFH) and citrate may be used as anticoagulant medication. To ensure treatment comparability between different patients, we will replace plasma in a fixed ratio of 1.2 × the individual patient’s total plasma fluid. The individual patient’s total plasma fluid will be calculated on each trial site from hematocrit and body weight (BW) following the formula by Kaplan et al. (16). The formula used calculates the estimated plasma volume (ePV) as: *ePV* = *[[0.065* × *BW* [kg]*)]* × *[100-Hematocrit* [%]*]]* × *10* [ml]. To avoid potential allergic reactions, anti-histamines (Clemastin (Tavegil®) 2 mg and Ranitidin (Ranitic®) 50 mg, both given as intra-venous (i.v.) push), will be administered before TPE (and in the control group at time of randomization). No additional cortisone push should be given as anti-allergic prophylaxis immediately before TPE treatment.

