#### Analyses of secondary endpoints

Analyses of the key secondary endpoints will be performed as follows:(i)The mean SOFA score will be analyzed as degree of organ failure measured by the per-patient mean daily SOFA score over 7 days. In case a patient dies before day 7, the daily SOFA score will be registered as 24 points for the following days until day 7. A linear regression model will be used for comparing the treatment arms, which includes mean daily SOFA score over 7 days as dependent variable, and treatment group, sex, pulmonary focus of infection (yes/no), baseline lactate (< 4.5/ ≥ 4.5 mmol/l), and center as independent variables. Superiority of the experimental intervention compared to the control intervention can be concluded if the upper boundary of the two-sided 95% confidence interval for the adjusted mean difference (experimental intervention minus control intervention) is below 0.A sensitivity analysis for the SOFA score will be performed using an exact test based on trimmed means [15]. This method follows the ITT principle in taking all randomized patients into account in the analysis without hypothesizing SOFA values for patients who die before day 7.(ii)Organ support-free days until day 28, determined as total days without need for invasive ventilation, vasopressor/inotropes, and RRT until day 28, will be analyzed similarly with a linear regression model with stratification factors of the randomization as co-variates. In case a patient dies before day 28, each remaining day until day 28 will be counted as a day with organ failure.

The confirmatory assessment of key secondary endpoints will be done in the above specified order as soon as the primary analysis of the primary endpoint is significant.

Other secondary endpoints:

The 90-day mortality (dead at day 90: yes or no) will be analyzed in line with the primary analysis of 28-day mortality. In addition, 28-/90-day mortality will be analyzed as time-to-event endpoint. The survival curves until day 28/90 will be estimated using the Kaplan–Meier method and compared using the log-rank test. Additionally, a Cox regression model will be utilized to estimate the hazard ratio between the treatment arms.

Other secondary endpoints (e.g., ICU length of stay, hospital length of stay, hemodynamics, arterial blood gas analysis) will be summarized by treatment group and compared with appropriate statistical tests.

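### The model for mean SOFA, the first confirmatory secondary endpoint, does not adjust for SOFA at inclusion, and its averaging window takes in the inclusion day

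*Protocol article*

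**What the plan says.** Outcomes, Key secondary endpoint, defines the endpoint as a SOFA average taken "over the first 7 days following randomization with day 1 (d1) indicating the day of study inclusion (i.e., the day of the intervention"). Its next sentence says that the score "will be recorded daily at inclusion and following the next 7 days", which is one reading at inclusion plus seven more.

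Statistical methods, Analyses of secondary endpoints, takes as outcome the "degree of organ failure measured by the per-patient mean daily SOFA score over 7 days". For deaths it states: "In case a patient dies before day 7, the daily SOFA score will be registered as 24 points for the following days until day 7". The linear regression has "treatment group, sex, pulmonary focus of infection (yes/no), baseline lactate (< 4.5/ ≥ 4.5 mmol/l), and center as independent variables". Inclusion SOFA is not in that list. On testing: "The confirmatory assessment of key secondary endpoints will be done in the above specified order", once the primary endpoint is significant. Mean SOFA is item (i), so it is tested first.

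On timing, the section on the treatment arm says: "The TPE treatment will be initiated within 6 h after randomization".

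**The concern.** Patients enter with differing degrees of organ failure. A mean SOFA over the following week carries that difference forward as noise unless the starting score is in the model. The protocol collects the starting score but does not adjust for it. The covariate list is written out in full, so this is a stated choice and not a detail left to an analysis plan.

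The inclusion day also counts as day 1 of the average. If the day 1 score is the reading taken before plasma exchange, treatment cannot have changed it, and it pulls the arm difference toward zero.

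At stake is the chance of confirming an effect on organ failure after a positive primary result, and how readable the reported SOFA difference is.

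**Working it through.** **The protocol's own figure.** The only sample size in the document concerns 28-day mortality (60% vs 42%, two-sided 5%, power 80%, continuity-corrected chi-square).
- Uncorrected: n₀ = [1.960·√(2·0.51·0.49) + 0.842·√(0.60·0.40 + 0.42·0.58)]² / 0.18² ≈ 119.9, so 120.
- Corrected: n = (n₀/4)·[1 + √(1 + 4/(n₀·0.18))]² ≈ 130.8, so 131 per group, as stated.

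Nothing comparable is given for SOFA. The 131 serves below only as the group size.

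**Days.** With d1 as the inclusion day, d1–d7 is the inclusion score plus six later ones. The recording sentence gives 1 + 7 = 8 scores. Take a patient with SOFA 14 at inclusion and on the next day, dead from the third day on:
- d1–d7: (14 + 14 + 5·24)/7 = 21.14
- all eight scores: (14 + 14 + 6·24)/8 = 21.50
- the seven after inclusion: (14 + 6·24)/7 = 22.57
- d2–d7: (14 + 5·24)/6 = 22.33

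**Dilution.** Suppose the d1 score precedes treatment and the daily effect δ is constant afterwards. The d1–d7 mean then shows 6δ/7, which is 14% less than δ.

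**Precision.** A baseline covariate multiplies the residual variance by 1 − R². This was simulated with 1,500 trials per setting and 131 patients per arm. All inputs are assumptions:
- SOFA SD 3
- a 0.5-point effect in survivors
- about 35% vs 25% dead within the seven days after inclusion, scored 24
- a correlation of 0.3, 0.5 or 0.7 between inclusion and later scores
- inclusion SOFA also predicts death (log-odds slope 0.3, 0.5 and 0.8 per SD respectively)
- inclusion reading unaffected by treatment

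| Correlation | R² of inclusion SOFA with the mean of later days | d1–d7, no baseline: effect, power | d1–d7, with baseline: effect, power |
|---|---|---|---|
| 0.3 | 0.066 | −0.96, 47.5% | −0.96, 51.8% |
| 0.5 | 0.166 | −0.91, 40.3% | −0.92, 51.7% |
| 0.7 | 0.308 | −0.90, 37.3% | −0.90, 53.5% |

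The gain from the covariate is about 4, 11 and 16 percentage points. For the mean of the later days, √(1 − R²) is 0.97, 0.91 and 0.83, so the confidence interval narrows by about 3%, 9% and 17%.

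**What the window adds once baseline is in the model.** Write the d1–d7 mean as (B + 6M)/7, with B the inclusion score and M the mean of d2–d7. In a regression that contains B, the treatment coefficient and its standard error are both 6/7 of those for M, so the test is identical. Only the scale of the estimate changes: −0.96·7/6 = −1.12, −0.92·7/6 = −1.07 and −0.90·7/6 = −1.05. A mean of all seven later days with the covariate gave 55–57% power, only 3 to 4 points more.

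**The case against.** The strongest reply is that the plan is coherent and the rest is preference.

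- **One window.** A start on d1, a length of seven days and a death rule that ends on day 7 all agree on d1–d7. Recording eight scores and averaging seven is not a contradiction. A reader might infer that the text contradicts itself, or that d1–d7 and d2–d8 would give different confirmatory results. The documents do not support either reading. The example shows that one patient's value moves with the set of days, not that a conclusion does. A d2–d8 outcome would also run past the day 7 death rule, and the biomaterial section lists visit 10 at day 7 and visit 11 at day 14, with nothing between. What stands against the plan is loose wording. The recording sentence reaches one day beyond the averaging rule, and Table 1 lists 0 and 12 h apart from d1–7 for other endpoints.
- **Day 1 may not be pre-treatment.** The protocol calls d1 the day of the intervention and does not say whether its score is a reading at inclusion or covers the day. This stands, so the 14% is conditional.
- **The model mirrors the primary one.** It uses the stratification factors, and lactate already captures some severity. True, and the simulation contains neither lactate nor the other factors, so the real gain could be smaller. But a two-level lactate variable is only a partial substitute for the starting value on the outcome's own scale, which is already collected.
- **The power figures are assumed.** This stands. With deaths scored 24, inclusion SOFA explained only 7% to 31% of the variance.

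**Conclusion.** The point holds as one of precision and clarity, not validity. Randomization keeps the SOFA comparison unbiased, and neither the missing covariate nor the inclusion day in the mean inflates the type I error. Both make a true effect harder to confirm.

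The main loss comes from the missing covariate: in the illustration, power is 37–48% as planned and 52–54% with inclusion SOFA added. Those levels rest on an assumed SD, effect, mortality and correlations. The direction rests only on inclusion SOFA being related to later SOFA or early death.

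The dilution of 1/7 applies only if the d1 score is the reading before plasma exchange. With the covariate in place it no longer affects the test, only the size of the reported difference. The endpoint is secondary and is tested only after a significant primary result, which limits the consequence.

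**What to change.** In Analyses of secondary endpoints, add the inclusion SOFA score as a continuous covariate to the linear model for mean SOFA. Use that score as baseline only, and define the outcome as the mean of the daily scores after inclusion through day 7, keeping the planned 24 points after death. Under the protocol's own d1 this is d2–d7, six scores, so the label of a 7-day mean needs rewording.

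State that the covariate is the reading from data before randomization. If the d1 score instead covers the day of the intervention, it is partly an outcome and must not serve as the baseline covariate.

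Reconcile the recording sentence in Key secondary endpoint with the day 7 limit in the death rule, so that only one set of days can be averaged.

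The cost is wording and one model parameter, fixed before arm-level data are seen. No new visit is needed, and sample size, randomization and the testing order do not change. The inclusion score must be complete for every patient.

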#### Secondary endpoints

As further secondary endpoints 90-day and 1-year mortality, intensive care unit length of stay (LOS), hospital LOS, (basic- and extended) hemodynamics, arterial blood gas analysis (BGA) parameters, respiratory-, renal- and liver function, sepsis associated coagulopathy, inflammatory response, cardiac function, and secondary infections will be analyzed (Table 1).

#### Safety endpoints

The following safety endpoints are assessed until day 7 following randomization (Table 1): bleeding complications, thrombotic complications, allergic reactions, infections related to the entry site of the dialysis catheter or new bloodstream infections, transfusion related lung injury, occurrence of, and time to severe thrombocytopenia (< 5.000/μl) and other device related serious adverse events (SAEs). Given the profound severity of disease in the patients under investigation (hospitalized patients under critical care, shock and (multi) organ failure) a variety of AEs and SAEs are expected to incept as part of the natural history of disease and will therefore not be reported. Furthermore, SAEs, that are not directly related to critical illness / sepsis per se and are classified as possibly, probably, or causally provoked by the intervention, will additionally be recorded until day 7. Potential SAEs that are directly related to critical illness will thus not be explicitly reported.

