Liver function 0 and 12 h, d1–7, ICU discharge	Bilirubin [µmol/l] Aspartate aminotransferase (AST) [U/l] Alanine aminotransferase (ALT) [U/l] Alkaline phosphatase (AP) [U/l] Gamma-glutamyl transferase (GGT) [U/l] Cholinesterase (CHE) [kU/l] Albumin [g/l]
Sepsis associated coagulopathy 0 and 12 h, d1–7	Differential full blood count (including hemoglobin (Hb) [g/dl], white blood cell count (WBC) [Tsd/µl], polymorphonuclear leucocytes (PMN) [Tsd/µl], lymphocytes [Tsd/µl], monocytes [Tsd/µl], platelets [Tsd/µl], and schistocytes [%]) Fibrinogen [g/l] D-Dimer [mg/l] International normalized ratio (INR) Lactate dehydrogenase (LDH) [U/l] Antithrombin (AT)-III [%] Protein C [%] vWF:Ag [IU/dl] (*only* at 0 and 24 h) ADAMTS13 [%] (*only* at 0 and 24 h) ISTH-DIC Score [0–8 points]
Inflammatory response 0 and 12 h, d1–7	C-reactive protein (CRP) [mg/l] Procalcitonin (PCT) [µg/l] Interleukin-6 (IL-6) [ng/ml] Ferritin [µg/l] Neutrophil/lymphocyte ratio
Cardiac function 0 and 12 h, d1–7, ICU discharge	Creatine kinase (CK) [U/L] Myoglobin [ug/L] NT-proBNP [ng/L] Troponin T, high sensitive [ng/L]
Secondary infections until ICU discharge	Presence [yes/no] Species [gram + /gram − /viral/fungal] Viral reactivation (HSV, EBV, and CMV copies by PCR) (*only* at days 7 and 14)
SAFETY ENDPOINTS	
Bleeding complications until day 7	Vascular access-related Intra cerebral bleeding Others
Bleeding complications until day 7	Acute myocardial infraction Thrombosis/ Embolism
Allergic reactions until day 7	Acute hemodynamic worsening + tachycardia
Infections until day 7	Infections related to the entry site of the dialysis catheter or new bloodstream infections
Transfusion associated lung injury (TRALI) until day 7	Significant worsening of respiratory function + typical X-ray deterioration
Severe thrombocytopenia until day 7	Occurrence of and time to severe thrombocytopenia (< 5000/μl)
Other device related Severe Adverse Events (SAEs) until day 7	Other device related SAEs such as air embolism or clot formation in the vein around the catheter with a risk of dislodgement of the clot to the lung
Other SAEs until day 7	SAEs that are not related to the critical illness / sepsis per se and are classified as possibly, probably or causally provoked by the intervention

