### Statistical methods

#### Analyses populations

The intention-to-treat (ITT) population comprises all randomized patients. Patients will be analyzed as randomized independently of the performed intervention. Primary analyses of all efficacy endpoints will be conducted on the ITT population.

The per-protocol (PP) population comprises all patients that received the randomized intervention and were complying with the study protocol until the end of the follow-up period. Supplementary efficacy analyses will be conducted on the PP population.

The safety population comprises all patients that received the study intervention. Patients will be analyzed as treated. Analyses of safety endpoints will be conducted on the safety population.

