#### Analyses of safety endpoints

Absolute and relative frequencies of all safety endpoint events will be displayed for the whole population and separately for experimental and control group and will be compared using chi-squared tests.

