## Discussion

To the present time, no adequately powered randomized clinical trial has investigated the effect of TPE on survival in septic shock patients. Previous studies investigating TPE in sepsis have either been underpowered or included a heterogenous study population [7, 8]. Therefore, despite promising data demonstrating more rapid hemodynamic stabilization [10, 14], the role of TPE as a potential adjunctive treatment option in septic shock remains unclear. As we have observed the most obvious clinical effects (during the feasibility trial) in sepsis patients that have been treated very early after onset of shock and that demonstrated particularly profound hemodynamic instability, we have designed the inclusion criteria of the here described study accordingly. This effort to homogenize the participants (early and severe septic shock) stands in contrast to previous trials that have investigated a broader range of septic patients.

TPE using human plasma as replacement fluid has potential adverse effects, including infectious and non-infectious (allergic reaction, transfusion associated lung injury (TRALI), citrate toxicity, hypotension) [16] with pruritus and urticaria most commonly observed [17]. However, severe adverse events are extremely rare [18] and incidence of adverse events requiring discontinuation of treatment lies at around 0.2% [17]. Of note, no adverse events were observed in our previous EXCHANGE feasibility pilot study [10] and the randomized EXCHANGE-1 trial, investigating patients with literally the same characteristics [19]. To avoid potential allergic reactions, anti-histamines will be administered before TPE (and in the control group at time of randomization). Importantly, there is no additional invasive exposure of the patient. The central line used for TPE will be inserted for clinical management (e.g., RRT) only and all biosamples will be drawn via catheters (central venous and arterial), which have been placed independent of biosampling for treatment and monitoring indication. Therefore, no additional puncture of the skin needs to be performed for biosampling.

The investigators convinced that a risk–benefit consideration clearly favors performance of the here proposed clinical trial. Importantly, this is an investigator-initiated trial, funded by the DFG without any competing commercial or financial interests involved.

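### For the Other SAEs row alone, the attribution rule leaves the control arm with few or no countable events, so the planned between-arm test of that row cannot be interpreted

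*Protocol article*

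**What the plan says.** The section Safety endpoints first lists events assessed to day 7 without any condition of attribution to plasma exchange: "The following safety endpoints are assessed until day 7 following randomization (Table 1): bleeding complications, thrombotic complications, allergic reactions", followed by infections, transfusion-related lung injury, severe thrombocytopenia and other device-related SAEs.

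It then deals with everything else. AEs and SAEs that belong to the expected course of the illness "are expected to incept as part of the natural history of disease and will therefore not be reported". Remaining SAEs must be unrelated to critical illness or sepsis, and only those that "are classified as possibly, probably, or causally provoked by the intervention, will additionally be recorded until day 7" are kept. The section closes: "Potential SAEs that are directly related to critical illness will thus not be explicitly reported". The Table 1 row Other SAEs until day 7 repeats the condition ("classified as possibly, probably or causally provoked by the intervention") and stands among the safety endpoints.

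The section Analyses of safety endpoints covers all safety endpoint events, shown for the whole population and "separately for experimental and control group and will be compared using chi-squared tests". The section Analyses populations defines the set to be used: "The safety population comprises all patients that received the study intervention", analysed as treated.

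The section Blinding states that the clinical team caring for the patient knows the allocation.

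**The concern.** A between-arm test needs events counted by the same rule in both arms. For the Other SAEs row, the rule refers to the treatment that only one arm receives. If the intervention is plasma exchange, a serious event in a control patient can hardly be classed as provoked by it, and it is therefore not recorded. The row then has no usable control rate.

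Two errors can follow. An apparent excess under plasma exchange can arise from the recording rule alone. In the other direction, a serious event that plasma exchange did cause, but that was read as sepsis and lies outside the named endpoints, is not recorded as an SAE in either arm. Attribution at the bedside is hard in septic shock, and the randomised comparison is the usual remedy. For this row the recording rule removes it. A later analysis plan cannot recover events that were never collected.

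**Working it through.** **1. Inputs.** From the protocol article: 274 patients randomised 1:1 (Sample size; allocation ratio under the consent heading), hence 274/2 = 137 per arm. Not given and therefore assumed: the true proportion of patients with a serious event outside the named list (r), and the fraction of such events in the plasma-exchange arm that is attributed to the intervention (f).

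**2. The plan's own figure.** Mortality of 60% versus 42%, two-sided 5%, 80% power:
- n = [1.960·√(2·0.51·0.49) + 0.842·√(0.60·0.40 + 0.42·0.58)]² / 0.18² ≈ 120 per group without correction
- with continuity correction, 131 per group, as stated.

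The sample size is not in dispute; it only supplies the arm size.

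**3. Which rows depend on attribution to the intervention?**

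| Safety row | Must be attributed to the intervention? | Can occur in controls? |
|---|---|---|
| Bleeding; infarction, thrombosis, embolism; allergic reactions; infections; lung injury; severe thrombocytopenia | No | Yes |
| Other device-related SAEs | No, but to a device | Yes: Eligibility criteria require suitable vascular access in every patient |
| Other SAEs | Yes | Hardly, if the intervention is plasma exchange |

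**4. How few events give a significant result?** For k of 137 against 0 of 137:
- Uncorrected: X² = 274k/(274 − k). For k = 4: 1096/270 = 4.06, p = 0.044. For k = 3: 822/271 = 3.03, not significant.
- Continuity-corrected: X² = 274(k − 1)²/[k(274 − k)]. For k = 4: 2466/1080 = 2.28, p = 0.13. For k = 6: 6850/1608 = 4.26, p = 0.039.
- Fisher's exact: p = 2·C(137,k)/C(274,k). For k = 4: 0.122. For k = 6: 0.030.

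So 4 attributed events suffice uncorrected, and 6 suffice with the correction or with Fisher's test.

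**5. Chance of a false excess when the true rates are equal.** The recorded count in the plasma-exchange arm is Binomial(137, r·f) and the control count is taken as 0.

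| r, both arms | f | Expected count (137·r·f) | P(≥ 4), uncorrected | P(≥ 6), corrected or Fisher |
|---|---|---|---|---|
| 5% | 10% | 0.7 | 0.5% | about 0 |
| 5% | 25% | 1.7 | 9.4% | 0.8% |
| 10% | 10% | 1.4 | 5.0% | 0.3% |
| 10% | 25% | 3.4 | 45% | 13% |
| 10% | 50% | 6.9 | 92% | 69% |
| 20% | 10% | 2.7 | 29% | 5.8% |
| 20% | 25% | 6.9 | 92% | 69% |
| 30% | 50% | 20.6 | 100% | 100% |

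The result depends only on the product r·f. A 10% rate with half attributed behaves exactly like a 20% rate with a quarter attributed, and the true control rate does not enter at all. That is the sense in which the test measures attribution.

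**6. With the same recording in both arms.** At equal true rates of 5% to 30%, the uncorrected test is significant in 4.8% to 5.1% of trials (2.3% to 3.7% with continuity correction).

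**The case against.** The best reply is that this is one row among about eight, recorded in addition to a substantial list of named endpoints, and that there is a reason not to report every expected event in patients with an assumed control mortality of 60%. A data safety monitoring board also reviews safety data. This stands, and it rules out several stronger conclusions that a reader might draw.

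- *That the whole safety comparison is void.* It is not. The named endpoints carry no attribution to plasma exchange and can be counted in controls.
- *That the control count is guaranteed to be zero.* The article does not define the intervention at this point, speaks of a control intervention in its primary analysis, and gives controls antihistamines at randomisation. Zero or nearly zero is as far as the text goes. Nor does it say who makes the attribution; that it will be unblinded staff is inferred from Blinding and from data entry at the sites.
- *That harm resembling sepsis is never counted.* New bloodstream and secondary infections, vasopressor doses, lactate, oxygenation, SOFA, organ support-free days and mortality are collected in both arms. What is lost is the record, as an SAE, of a serious event outside the named list.
- *That the chi-squared test is wrong because the protocol expects sparse data.* The remark that "severe adverse events are extremely rare" summarises literature on plasma exchange; it does not predict event rates in this trial. An exact fallback is ordinary analysis-plan detail. Fisher's test would not help here either, because it has no valid control rate to work with.
- *That controls are excluded from the safety population.* The literal wording suggests it, but analysis as treated and a displayed control group point the other way. This is a wording conflict. Analysing safety as randomised instead of as treated would be a preference.

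The reply does not rescue the row itself. It is listed as a safety endpoint, and all safety endpoints are to be tested.

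**Conclusion.** The point holds for the Other SAEs row only. Its recording rule and the stated between-arm test do not fit together, so the comparison is uninterpretable whatever the true effect. Four attributed events against none would already reach p = 0.044 uncorrected. Over the assumed rates (5% to 30%) and attributed fractions (10% to 50%), the chance of a spurious significant excess runs from 0.5% to 100% uncorrected, and from about 0 to 100% with continuity correction. This range shows that the result is governed by attribution; it is not a forecast.

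The conclusion assumes that the intervention means plasma exchange, that the row is tested as the text says, and that control events are rarely or never attributed. The primary and key secondary endpoints and the named safety endpoints are unaffected. This should be fixed, but it does not threaten the trial's main result.

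**What to change.** **At minimum (wording of the analysis only):** report intervention-attributed Other SAEs for the plasma-exchange arm alone, as a count and proportion with an exact confidence interval and no between-arm test. Base the randomised safety comparison on the endpoints ascertained alike in both arms.

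**Preferably:** record SAEs to day 7 by the same criteria in both arms, with relatedness as a separate field. The row can then be compared between arms, and the attributed subset can still be described.

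**In either case:** state what the intervention means in this rule, and reword the safety population so that it explicitly includes control patients, in line with the planned comparison.

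**Cost:** the minimum change and the rewording cost nothing in data collection. The preferred change means more eCRF entries and, because SAEs are also documented on paper, more paper forms in a critically ill population. The article states that no patient had yet been recruited, so the change could be made before data collection began; it cannot be made retrospectively for events that were not recorded.
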